### Data management

2.7

The data are collected and evaluated in pseudonymized form at the Institute for Psychosocial Prevention at the Heidelberg University Hospital, Germany. This involves using a code instead of specifying names. A paper coding list links the names to this code. Access to this coding list is restricted to the study coordinator (SP) and the principal investigator (ST). Once the evaluation is complete, the coding list will be deleted by 31 December 2026 at the latest. The data will then be anonymized. This anonymized data will be stored for at least 10 years after the evaluation or the publication of a paper based on this study. Only project staff involved in data collection and analysis, such as research assistants, have access to the pseudonymized data and the final anonymized dataset. Data collection is conducted via the online survey tool SoSci Survey (Leiner, 2024). Paper-and-pencil questionnaires are also entered into the system and then securely destroyed. SoSci Survey does not claim ownership of the questionnaires and will neither use nor disclose the data for its own purposes. Confidentiality is a prerequisite for project staff in order to ensure data security. No risks are expected to arise from participation. Participation is voluntary and requires informed consent. It can be withdrawn at any time without any disadvantages. For minors, informed consent must be provided by their legal guardians.

### Statistical analysis

2.8

Data will be analyzed using the intention-to-treat approach. Multiple imputation will be used to impute missing values. We will analyze and report on attrition. We will check for possible correlations between our variables, primary and secondary outcomes, as well as sociodemographics, and dropout at different time points. Additionally, we will report the reasons given by parents or children for withdrawal. The main analysis is a multilevel analysis due to the nested data structure (children in school classes). Both inter- and intraindividual differences and changes are analyzed. Demographic variables will be included in the data analysis model to control for group differences at baseline. In addition, we will examine a possible mediating effect of increased mental health literacy on increased help-seeking behavior through reduced stigma using multilevel mediation analysis. In addition, we will use correlational analyses as well as chi-squared tests, *t*-tests, Mann–Whitney-U-tests and *F*-tests for group comparisons and comparisons across time points. A significance level of *α* = 0.05 will be used. To validate the newly constructed mental health literacy scale, exploratory factor analysis (EFA) will be conducted, and the comparability of the three vignettes will be checked using ANOVAs. Qualitative data will be analyzed using Mayring’s content analysis using both deductive and inductive approaches (Mayring, 2015). On the one hand, the responses will be matched (deductively) to a pre-established coding scheme to indicate the extent to which the mental health problem is understood by the participating children, and the appropriateness of the help offered by the child. The children’s responses will be grouped blindly by two independent assessors. In the case of discrepancies, the scores will be discussed. On the other hand, categories will be formed (inductively) from the answers to gain more precise insight into the content of the children’s answers.

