**Methods:**

In this study, the “Talking mental health” (TMH) prevention program is evaluated using a cluster-randomized design, comparing an intervention group with a waitlist control group. The primary outcomes are mental health literacy, stigma and help-seeking behavior. Measurement takes place pre and post, as well as at a six-week follow-up. The sample size aims for 35 school classes with approximately 525 parents and children. The study also examines the effects of an additional parent training on children’s and parents’ mental health.

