To assess mental health literacy children are presented with one of three case vignettes, with a different case vignette presented at each time point of the survey. The order in which each vignette is presented to each child is counterbalanced by intraindividual block randomization to avoid possible sequence effects. The three case vignettes used are self-designed cases based on the vignettes used to measure mental health literacy by Jorm et al. (1997). The case vignettes are similar to Jorm’s vignettes in that the case is a description of a situation in which mental distress or illness can be identified. However, in contrast to Jorm’s case vignettes, the case vignettes used here portray three children (Noah, Kim, Conny) rather than adults as affected. The three names were chosen to be gender neutral. In Noah’s case, symptoms of depression are described; in Kim’s case, symptoms of attention deficit hyperactivity disorder are described; and in Conny’s case, symptoms of conduct disorder are described. For each case vignette, there are two open questions and 14 closed questions. The open questions are, “What do you think is Noah’s [Kim’s/Conny’s] problem?” and “What do you think would be the best way to help Noah [Kim/Conny]?” The closed questions relate to the assessment of the severity and origin of the stress, as well as the assessment of self-help strategies in the situation described: E.g., “Do you think Noah [Kim/Conny] might have a mental health problem?” or “What do you think could improve Noah’s [Kim’s/Conny’s] situation - If Noah [Kim/Conny] stayed at home? Children respond using a simplified 3-point Likert scale (1 = Yes, 2 = Maybe, 3 = No), adapted to their cognitive and developmental level. The case vignettes were first tested for comprehension in a fourth grade-class, in which n = 22 children commented on the comprehensibility and were subsequently revised. Question wording and selection were based on theoretical considerations of the knowledge component of mental health literacy, items from a validated adult mental health literacy questionnaire (MHLq-SVa; Campos et al., 2022), and consultation with experts in the field to ensure item content validity.

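### Mental health literacy is measured with a different disorder vignette at each wave, but the only stated handling of vignette is an ANOVA check; modelling it would recover precision at almost no cost

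*Protocol article*

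**What the plan says.** The Abstract (Methods) lists the outcome among the primaries: "The primary outcomes are mental health literacy, stigma and help-seeking behavior". Hypothesis 1a in the Introduction rests on it, and it is the first link in the mediation chain of Hypothesis 1e.

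Section 2.6 (Outcome measurements) says that "children are presented with one of three case vignettes, with a different case vignette presented at each time point of the survey". The three cases describe different disorders: depression, conduct disorder, and one in which "symptoms of attention deficit hyperactivity disorder are described". Order is controlled: "The order in which each vignette is presented to each child is counterbalanced by intraindividual block randomization to avoid possible sequence effects". On content, "For each case vignette, there are two open questions and 14 closed questions".

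Section 2.8 (Statistical analysis) specifies a multilevel model of children in classes, with demographic variables included because of possible baseline differences between groups. It says that both differences between children and changes within children will be analysed. Vignette appears once, in the sentence on scale validation: "the comparability of the three vignettes will be checked using ANOVAs". The same sentence says: "To validate the newly constructed mental health literacy scale, exploratory factor analysis (EFA) will be conducted".

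**The concern.** A child's score at a given wave depends partly on which disorder was shown. Recognising depression and recognising conduct disorder may not be equally easy for an 8- to 10-year-old. Since the vignette changes at every wave, a child's change over time combines real change with the difference in difficulty between two cases.

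The ANOVA does not deal with this. A non-significant result would not show that the vignettes are equivalent, and a significant one has no stated consequence. If vignette then stays out of the main model, its contribution remains in the residual. That widens the confidence interval for a primary outcome. In the mediation analysis it adds noise to a predictor, which pulls the estimated path towards zero.

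**Working it through.** **Inputs from the article.** 35 classes of 15 children (sections 2.2 and 2.3); 35 × 15 = 525, which matches the Abstract. Three vignettes, one per wave, without repetition (section 2.6). The article gives no vignette means, intraclass correlation or within-child correlation.

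**Assumptions.** Vignette means of 0, g/2 and g in SD units, so g is the gap from easiest to hardest. Within-child correlation r = 0.5, class intraclass correlation 0.05 and, for power, a true effect of 0.3 SD.

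**Step 1: child-level change.** The variance of the three means is v = g²/6. Two waves show two different vignettes. Drawing without replacement from three gives a covariance of −v/2, so the difference carries 2v + v = 3v. The change-score variance is multiplied by [2(1 − r) + 3v] / [2(1 − r)].

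| g | v | 3v | variance ratio | square root |
|---|---|---|---|---|
| 0.3 | 0.015 | 0.045 | 1.045 | 1.022 |
| 0.5 | 0.0417 | 0.125 | 1.125 | 1.061 |
| 1.0 | 0.1667 | 0.500 | 1.500 | 1.225 |

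At g = 1.0 the variance ratio is 1.417 for r = 0.4 and 1.625 for r = 0.6.

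**Step 2: treatment effect, baseline-adjusted.** Simulation of 35 × 15 children, 1,000 runs per row, true effect 0.3 SD, with and without vignette terms for both waves.

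| g | SE without | SE with | ratio | power without | power with | mean estimate (without / with) |
|---|---|---|---|---|---|---|
| 0 | 0.0836 | 0.0840 | 0.995 | 0.935 | 0.930 | 0.300 / 0.299 |
| 0.5 | 0.0875 | 0.0825 | 1.061 | 0.895 | 0.931 | 0.293 / 0.293 |
| 1.0 | 0.0994 | 0.0828 | 1.200 | 0.812 | 0.940 | 0.297 / 0.298 |

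The null runs give similar ratios: 0.0864/0.0821 = 1.05 at g = 0.5 and 0.0984/0.0793 = 1.24 at g = 1.0. Type I error without vignette terms was 0.041, 0.049 and 0.049 at g = 0, 0.5 and 1.0. The gap of 0.3 SD was not simulated; step 1 points to about 2% on the SE.

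**Step 3: treatment effect from post scores only.** SE = √{(4/35) × [ICC + (1 − ICC + v)/15]}. With ICC = 0.05, the SE ratio is 1.004, 1.012 and 1.048 at g = 0.3, 0.5 and 1.0. Power is 0.747, 0.740 and 0.711, against 0.750 with no gap. With ICC = 0.20 the SE ratio at g = 1.0 falls to 1.022, because variance between classes dilutes the effect.

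**Step 4: literacy-to-stigma path.** The stigma scale does not use the vignettes. If vignette adds noise to literacy change and leaves stigma untouched, the child-level slope shrinks by the inverse of the step 1 ratio: 1/1.045 = 0.96, 1/1.125 = 0.89 and 1/1.5 = 0.67.

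**Step 5: factor analysis.** Null simulation of 14 items with three factors and 525 independent children, 3,000 runs. Type I error was 0.049 for a fixed sum score, 0.055 for the first factor taken blind to arm, and 0.151 when the best of three factors was picked after seeing results by arm.

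**The case against.** The strongest objection is that this reads a decision into silence. The sentence on demographic variables is not a closed list of model terms, and a full analysis plan, which is not shown, may contain a vignette term. That stands in part: the article does not say vignette is left out. What it does state is the ANOVA, and a comparability check cannot do the work of a model term.

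Three stronger readings are tempting, and the documents do not support them.

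- **That the treatment effect is biased.** Counterbalancing within each child (section 2.6) prevents this. The simulated estimates were close to the true 0.3 in every row, with type I error near nominal.
- **That post-treatment data will shape the primary score.** Section 2.8 gives validation as the purpose of the factor analysis and says nothing about choosing or dropping items. Section 2.6 says question selection rested on theory, a validated adult questionnaire and expert advice. The article does not say which waves enter or whether the analyst is blind to arm, and it gives no scoring rule for the closed items. That leaves a risk open but is not an error in the text. Only an unblinded choice among factors inflated the type I error, and nothing in the article proposes one.
- **That the loss is as large as the vignette share of change-score variance.** At a 1.0 SD gap that share is 0.5/1.5 = 33%, but it describes a child's raw change, not the treatment comparison.

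It is also fair to say that the ANOVA is informative about the instrument. Removing it, or limiting the factor analysis to baseline data, would be a matter of preference.

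**Conclusion.** The point holds as an improvement in precision that costs almost nothing. A primary outcome carries a known, recorded source of variation, and its only stated handling is a check that cannot establish equivalence and leads to no action.

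The loss depends on a gap that the article does not report. It is negligible at about 0.3 SD. In a baseline-adjusted analysis it is about 6% of the standard error at 0.5 SD and 20% at 1.0 SD. At an effect of 0.3 SD, those correspond to power of 0.895 instead of 0.931 and 0.812 instead of 0.940. An analysis of post scores alone would lose less (1.2% and 4.8%). The mediation path would shrink to roughly 0.89 or 0.67 of its value at the two larger gaps, on a simple child-level change-score argument.

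All values of g, r, the intraclass correlation and the effect are assumptions. The simulation clusters by class only; further variance between schools would reduce the percentage loss.

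**What to change.** In section 2.8, or in the analysis plan, state that the vignette seen at each wave enters the mental health literacy model as a three-level fixed effect (2 degrees of freedom), whatever the ANOVA shows. If the baseline score is used as a covariate rather than as a repeated outcome, its vignette should be entered too, at 2 further degrees of freedom. Apply the same adjustment to the literacy variable in the mediation model for Hypothesis 1e, and carry vignette in the imputation model for literacy. The ANOVA can stay as a descriptive check.

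As a secondary safeguard, state that the factor analysis is run blind to arm, and that the item set, item direction and scoring of the closed questions are fixed before any analysis by arm.

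This needs no new data, because each response already belongs to a known vignette. If the vignettes prove equal, the cost is a few degrees of freedom: power was 0.930 with the terms and 0.935 without, a difference within simulation error.

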## Discussion

3

Mental disorders are prevalent in elementary school-aged children (Morrison Gutman et al., 2015). Increased stress among children due to the COVID-19 pandemic (Ravens-Sieberer et al., 2022), long waiting times for therapy for existing mental disorders (Singer et al., 2022), numerous negative consequences of mental disorders (e.g., Shaw et al., 2012; Asselmann et al., 2018), and low mental health literacy among children and parents (Reardon et al., 2017; Tharaldsen et al., 2017) highlight the urgent need for early prevention approaches to improve mental health in schools. However, to date, most prevention approaches have focused only on older children or parents (Ma et al., 2023a). Therefore, the aim of this study is the evaluation of the prevention program “Talking mental health” tailored for 8–10-year-old school children in Germany. This program teaches children in a playful way what mental health is and how to distinguish between big and small feelings. It helps children understand when they need to seek help (when big feelings are present), from whom they should seek help, and when their coping strategies (toolbox), e.g., reading, journaling, and bathing, are sufficient (when small feelings are present). Children learn to talk about how they feel and learn to listen. Parents learn where to seek help, what services are available for specific problems and how to talk to their children about their feelings. These activities aim to increase mental health literacy, reduce stigma and encourage help-seeking behavior. The project also goes a step further by offering parents psychological counseling and evidence-based parenting training.

The strength of this prevention program is that it can be carried out by student volunteers. This means that teachers and school social workers do not incur any additional costs or burdens. Moreover, both groups can participate in the intervention and build on it. If effective, this would provide a scientifically tested prevention program for elementary schools that could be implemented cost-effectively on a larger scale. As a result, families may be more likely to take advantage of the care structures in place, thus reducing the risk of chronicity.

In addition to a universal prevention approach, we also offer an indicative prevention approach for particularly burdened families. In this way, the project also contributes to reducing psychological stress in children and their families.

It is often difficult to carry out randomization in the school context, which is why many evaluation studies in this area only use a quasi-experimental design. However, our design, with a waiting list control group, seems to be an appropriate and ethically acceptable approach. Nevertheless, there are a number of methodological and practical challenges associated with this study and with school-based prevention for children in general.

We developed our own vignettes, as we were not aware of any established instruments for measuring mental health literacy in children aged 8–10 years. The stigma measure (PMHSS; McKeague et al., 2015) was tested only with children aged 9 + years. In agreement with the authors, we also used it with 8-year-olds. We also support the children by having at least one project worker present during the surveys. The children can ask questions, and any unfamiliar words are explained.

In addition, the planned intervals between surveys vary slightly between schools because of holidays or internal school processes. However, we ensure that there is at least 1 week between survey 1 and 2 and at least 6 weeks between survey 1 and 3.

This first evaluation of the prevention program measures effects only after 6 weeks and therefore captures only short-term outcomes. If there is early evidence of effectiveness, then long-term effects should also be part of the evaluation in future studies.

Past studies have shown that children may not benefit equally from interventions designed to promote well-being. In one study, some children did not benefit from a mindfulness-based intervention, and others even showed a decrease in well-being (Kuyken et al., 2022). The authors argued that mindfulness exercises may have directed attention to unpleasant emotional states, that teachers may not have implemented the intervention adequately, or that additional strategies for coping with stress might have been necessary (Kuyken et al., 2022). In our “Talking mental health” school lessons, discussions about feelings and mental health may also potentially reactivate existing stress or unpleasant emotional states in children. Therefore, during lessons, we continuously monitor the children’s stress levels using the “mood barometer.” Children always have the option to leave the room together with the teacher or a trained student conducting the lesson. The students delivering the lessons are specifically trained to handle such situations. Additionally, a toolbox for dealing with different emotions is developed collaboratively with the children. At the end of the program, parents are offered the opportunity to attend a psychological consultation. During this meeting, any open questions can be addressed, and parents and children can be referred for further support if needed. Overall, the benefits of participating in the lessons clearly outweigh any potential risks.

In our study, we primarily relied on self-reports. In this young age group, such reports may be influenced by social desirability or other response biases (Soneson et al., 2025; Wang and Zang, 2025). Mental health stigma (Kaushik et al., 2016) or concerns regarding data security (Soneson et al., 2025) may prevent children from openly reporting whether they are seeking help or have mental health difficulties. Similar issues, including stigmatization and shame, have also been described in the context of self-reported bullying assessments (Furlong et al., 2010). In accordance with the recommendations by Wang and Zang (2025), we used neutral wording and avoided leading questions. Prior to the interview, we informed the children that their answers would be treated as strictly confidential and recorded using a number–letter code instead of their names. We also reminded them that there were no right or wrong answers. We did not include social desirability detection items or validity screening items, which should be considered in future research (Cornell et al., 2012; Wang and Zang, 2025).

In addition, only schools in the Heidelberg area are included in this first evaluation study (convenience sampling method). The socioeconomic status in Heidelberg is above German average. Therefore, we consider the influence of socioeconomic status and migration background in our evaluation. It should be noted that, so far, 12 of the 28 schools contacted have expressed interest in participating in the study. Possible differences between participating and non-participating schools will be examined and reported after data collection in order to identify possible biases. When interpreting the findings, it is important to note that the results may not be representative or generalizable. This study should therefore be understood as an initial evaluation in the German-speaking context. Future research should implement the intervention in more rural areas and different countries.

Due to the small number of recruited schools, and for reasons of model parsimony and statistical power, we have decided not to include the school as an additional level in our main model. In exploratory analyses, we will examine variance at the school level to determine whether these differences can explain treatment effects. Due to data governance regulations, specific information at the school level, such as exact distributions of migration background and socioeconomic status, is currently not available. However, publicly accessible data from the relevant local administrative districts may serve as a reference.

This study will provide valuable insights into the effectiveness of the “Talking mental health” program in increasing mental health literacy and help-seeking behavior and in decreasing stigma. In addition, analyzing satisfaction ratings and reasons for withdrawal will offer important information regarding the acceptance and future implementation of such programs.

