### Design and randomization

2.1

This study evaluates the “Talking mental health” prevention program using cluster randomization with a pre-post follow-up measurement approach. Elementary schools are randomly assigned to either the experimental condition or the waitlist control group by the study coordinator (SP) using digital coin toss^1^. The assignment is documented in an electronic file. Neither stratification nor block randomization are applied. The participants in the experimental condition are instructed to complete a questionnaire just before the prevention program. The post-measurement takes place at least 1 week after the intervention, and the follow-up at least 6 weeks later. In comparison, all three measurements in the waitlist control group are taken at the same time intervals, but the intervention takes place only after the last measurement.

A quasi-experimental design is used for the group of college students who carry out the prevention program. We compare students from the student organization “Vitaphilie” (Medical Students’ Association of the Heidelberg University), who are trained to deliver the program, with students from other medical student organizations not trained in the program. The students assign themselves to the student organizations independently (quasi-experimental; students carrying out the training vs. students from other student organizations).

Upon request and if needed, a psychological counseling session for the parents and subsequent parent training are offered after completion of the project (parent skills training based on EFST-P; Dolhanty et al., 2022). Parents are surveyed before and after the training, and 4 months later, and compared with parents who did not receive the training (quasi-experimental allocation).

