### Power

2.3

The sample size of the study was determined by taking into account recommendations based on model analyses, which suggested that 35 classes of 15 students were needed to measure a moderate effect in a three-level design (Kerkhoff and Nussbeck, 2019).

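### Schools are randomised but the main model stops at class level, so any between-school variance makes the treatment standard errors too small and lifts the type I error above 5%

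*Protocol article*

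**What the plan says.** Section 2.1 (Design and randomization) sets the unit of allocation: "Elementary schools are randomly assigned to either the experimental condition or the waitlist control group by the study coordinator". Allocation is by digital coin toss, and "Neither stratification nor block randomization are applied". All participating classes of a school therefore share one condition.

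Section 2.8 (Statistical analysis) sets the model: "The main analysis is a multilevel analysis due to the nested data structure (children in school classes"). The significance level is 0.05.

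Section 3 (Discussion) confirms that the missing level is deliberate: "we have decided not to include the school as an additional level in our main model". The reasons given are the small number of schools, parsimony and power. School variance is left to exploratory analyses.

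Three other statements bear on the point:
- Section 2.3 (Power) counts classes: "35 classes of 15 students were needed to measure a moderate effect in a three-level design". No number of schools enters.
- The only indication of the number of schools is in the Discussion, where "12 of the 28 schools contacted have expressed interest in participating in the study" at the time of writing.
- Section 2.8 also says "we will use correlational analyses as well as chi-squared tests", together with t-, Mann-Whitney and F-tests for group comparisons, without linking them to particular hypotheses.

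**The concern.** With allocation by school, the arm difference is a difference between two sets of schools. Whatever makes one school's children score differently from another's goes straight into that difference. A model whose highest level is the class treats each class as a separately randomised unit and leaves this component out of the standard error.

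The stated reasons do not help. Few randomised units is the situation in which the inference most needs to reflect them, and power gained by counting classes in place of schools is precision the design does not have. An exploratory estimate of school variance leaves the main p-value as it was. With about a dozen schools, a small or non-significant estimate would not show that the level can be ignored.

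The document itself gives reasons to doubt zero school variance. Survey intervals differ between schools because of holidays and internal processes (Discussion). Tablet or paper completion depends on what the school has (section 2.4). Both could affect change as well as level. At stake are the randomised comparisons for children (H1a-d) and parents (H2a-b).

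**Working it through.** **The plan's own figure.** 35 classes × 15 children = 525, as the Abstract states. The power behind it cannot be recomputed, because the article gives no numeric effect size, power or ICC. An article may leave those to the full protocol, so that is not counted against it.

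**Inputs from the document.** Unit of randomisation: school (2.1). Highest modelled level: class (2.8, Discussion). Classes: 30 done + 6 planned = 36 (3.1). Schools: 12 interested so far (Discussion), hence 36/12 = 3 classes per school. Children per class: 15 (2.2, 2.3). Alpha: 0.05 (2.8).

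**Assumptions.** All 12 schools take part, split 6:6; two-sided test; total variance 1; class ICC c = 0.05; school ICC s from 0 to 0.10. A t-test on class means stands in for the class-random-intercept model, to which it is equivalent in balanced data.

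**Formulas.** Let e = 1 − s − c, and let u = c + e/15 be the variance of a class mean within its school.

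- True variance of an arm mean (6 schools × 3 classes): V = (s + u/3)/6.
- Variance the class-level analysis estimates on average (18 classes treated as independent): N = (u + s × 15/17)/18. The factor 15/17 arises because 18 classes from 6 schools have an expected sum of squares of 17u + 15s on 17 degrees of freedom.
- Ratio of true to reported standard error: r = √(V/N).
- Approximate type I error: P(|t| > 2.032/r) on 34 degrees of freedom.

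**Example at s = 0.05.** u = 0.05 + 0.90/15 = 0.11. V = (0.05 + 0.11/3)/6 = 0.01444. N = (0.11 + 0.05 × 15/17)/18 = 0.00856. r = √1.687 = 1.30. The effective cut-off is 2.032/1.30 = 1.56, giving about 12.7%.

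| School ICC | V | N | r | Type I error, formula | Type I error, simulation |
|---|---|---|---|---|---|
| 0 | 0.00630 | 0.00630 | 1.00 | 5.0% | 5.0% |
| 0.01 | 0.00793 | 0.00675 | 1.08 | 6.9% | 6.8% |
| 0.02 | 0.00956 | 0.00720 | 1.15 | 8.7% | 8.7% |
| 0.05 | 0.01444 | 0.00856 | 1.30 | 12.7% | 12.7% |
| 0.10 | 0.02259 | 0.01083 | 1.44 | 16.9% | 17.2% |

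A separate simulation with 40,000 runs per cell gave 6.8%, 8.7%, 12.8% and 17.7% at the four non-zero ICCs. In the same runs, a test on school means with K − 2 degrees of freedom (K schools) stayed at 4.8% to 5.3% in every scenario.

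**Sensitivity to the number of schools.** At school ICC 0.01, 0.02, 0.05 and 0.10, simulated error is 6.0%, 6.9%, 9.0% and 11.4% with 18 schools × 2 classes, and 7.9%, 10.8%, 17.0% and 23.4% with 8 schools × 4 classes. Neither count is in the document; they bracket 12.

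**Detectable effect with schools as the unit.** The standard error of the difference is √(2V). For 80% power on 10 degrees of freedom the multiplier is about 3.11. At s = 0.05: 3.11 × √0.02889 = 3.11 × 0.170 = 0.53 SD.

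| School ICC | Detectable effect (SD) | Power if true effect is 0.5 SD |
|---|---|---|
| 0 | 0.35 | 0.98 |
| 0.01 | 0.39 | 0.95 |
| 0.02 | 0.43 | 0.90 |
| 0.05 | 0.53 | 0.76 |
| 0.10 | 0.66 | 0.57 |

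**The case against.** **The size is assumed.** No school ICC is given, and at zero there is no inflation. The planned model also covers change over three waves with demographic covariates, so the relevant quantity is between-school variance in change or adjusted outcome, which may be smaller than the raw ICC. This stands. A reader might infer that the false-positive rate is well above 5%; the document does not support that as a fact.

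**The simple tests are not assigned to the randomised hypotheses.** A reader might infer that H1 and H2 will also be tested with unclustered t- or chi-squared tests. Section 2.8 does not say so. The trial has other uses for them: the non-randomised student and parent-training comparisons, attrition, and participating versus non-participating schools. This stands too, so the criticism applies only where such a test compares the randomised arms.

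**A moderate effect may still be detectable.** A reader might infer that a valid analysis cannot detect one. Taking moderate as 0.5 SD (the document gives no number), school-level power is 0.90 at school ICC 0.02 and still 0.80 at 0.04. The categorical claim fails.

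**Other inputs are uncertain.** Twelve is a count of interested schools. A 6:6 split is one outcome of unblocked tossing, with probability 924/4096, about 23%. An 8:4 split would raise the true variance of the contrast by (1/8 + 1/4)/(1/6 + 1/6) = 1.125.

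**Parsimony is a fair modelling aim.** It can be met by analysing school summaries, which is simpler still. It does not justify inference at a level below the randomised one.

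None of these objections removes the mismatch between allocation and model.

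**Conclusion.** The concern holds in conditional form. The main analysis omits the unit that was randomised, by declared choice, and the exploratory analysis does not repair the main test. Any positive between-school variance in the baseline-adjusted outcome makes the treatment standard error too small.

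Under the illustrative layout the inflation runs from none, through mild at school ICC 0.01, to roughly two and a half times the nominal rate at 0.05 and more than three times at 0.10. These figures rest on the assumed ICCs, 12 schools, equal cluster sizes, a 6:6 split and a single post-intervention comparison of children. They show the order of the problem and do not predict the trial's actual error rate. Because every randomised hypothesis depends on this model, it should be corrected before the arms are compared.

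**What to change.** 1. In section 2.8 and the Discussion, base the primary inference for H1a-d and H2a-b on the school. Either fit random intercepts for school, class and child with small-sample degrees of freedom (Kenward-Roger or Satterthwaite), or use a school-level analysis or a permutation test that re-allocates whole schools. Only the school-mean test was verified here. The mixed model was not evaluated successfully because too few simulated fits converged, so a school-level analysis should be named as the fallback.
2. Adjust for the t1 value of the outcome, which recovers part of the precision the authors were concerned to protect.
3. Keep the class-only model as a sensitivity analysis.
4. Where a chi-squared, t-, Mann-Whitney or F-test compares the randomised arms, label it descriptive or replace it with the clustered model.
5. In section 2.3, state the number of schools and the detectable effect with schools as the unit over a shown ICC range, as in the second table above.

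**Cost.** The change is to analysis wording only, with no new data. The price is wider intervals and a less favourable stated detectable effect.
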